## Methods

### Trial design

The prospective, parallel, single-blind, randomized controlled trial will evaluate the effects of different conditioning methods of TCHE on lung function in middle-aged and elderly people. It fulfills the requirements of the Standard Protocol Items: Recommendations for Interventional Trials (SPIRIT) checklist [23].

The subjects will be recruited from Mengcheng County, Anhui Province, China. A simple randomization will be used to divide them into a breath regulation group, body regulation group, heart regulation group, and control group in a 1:1:1:1 proportion. The subjects in the control group will receive health education only and maintain their previous lifestyle, and the three experimental groups will undergo exercise intervention (including warm-up, relaxation, and stretching) and health education for 6 months, 5 times a week, with each session lasting 60 min. The main and secondary results will be tested at baseline and at 3 and 6 months after the beginning of the intervention. An overview of the research program flow is presented in Fig. 1. The SPIRIT flow chart of the time points for enrolment, interventions, and assessments is shown in Fig. 2.

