### Sample size calculation

Considering the results of a previous study that used forced vital capacity (FVC) as the primary outcome index [24], the sample size was calculated by one-way ANOVA in Power Analysis and Sample Size version 15.0.5 (PASS 15.0.5 NCSS, LLC, USA). With a power of 80%, an alpha of 0.05, a standard deviation of 48, a standard deviation of the means of 8.16, and a dropout rate of 20%, we aim to recruit a minimum of 120 subjects per each of the four groups.

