### Outcomes

The changes of pulmonary function from baseline to the end of the interventions will be assessed using the pulmonary function evaluation system (MasterScreen, Germany). The main outcome measure is forced vital capacity (FVC), and the secondary outcome measures are the forced expiratory volume in 1 s (FEV1), FEV1/FVC ratio, vital capacity (VC), and maximal voluntary ventilation (MVV). All results will be evaluated at baseline and 3 months and 6 months after the intervention by the same evaluator. The test will be conducted in a room with good ventilation and constant temperature and air pressure to minimize the influence of confounding variables on lung function [37].

The pulmonary function of the patients will be evaluated according to the standards of the American Thoracic Association/European Respiratory Association (ATS/ERS) [38]. Technicians will be required to skillfully grasp the correct operation of the inspection items and have a good service attitude. In the process of inspection, technicians will verbally and non-verbally encourage participants to complete the inspection. Before the test, the technician will explain the purpose and method of the lung measurement examination to the participants. In order for the participants to understand the task of completing maximal inhalation and exhalation, the technicians will demonstrate the proper technique. The height, weight, name, age, and other parameters of the subjects will be recorded. For the measurements of height and weight, subjects will be asked to be barefoot and use light clothes. The subjects will be standing, and the height of the instrument will be adjusted to maintain the head in a front-facing position. During the test, a mouthpiece will be wrapped tightly with the lips, and the nose will be held with both hands to avoid air leakage. Next, the technicians will instruct the participants to inhale or exhale and to avoid coughing or repetitive breathing throughout the exhalation or inhalation without interruption. The test will be conducted from 9 to 11 am to avoid the changes in individual lung function that occur throughout the day.

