### Statistical methods

The SPSS statistics software (IBM SPSS STATISTICS, 25.0 version, Armonk, NY) will be used for data analysis and statistical testing. The Kolmogorov-Smirnov test will be used to check whether the data conform to the normal distribution. The average ± standard deviation (SD) will be used to describe continuous variables, and categorical variables will be expressed as *n* (%). Paired sample *t*-test will be used for intra-group comparison, and one-way analysis of variance (ANOVA) and covariance analysis will be used for inter-group comparison. The homogeneity of variance will be tested before ANOVA followed by a comparison of between-group variability using the least significant difference method corrected for test level *α* using Bonferroni adjustment.

Covariance analysis will be used to control other non-interventional factors. Repeated measurement analysis of variance will be used to analyze the intervention effect at different intervention times. The statistical difference may be significant (if *P* < 0.05) and very significant (*P* < 0.01).

All missing data will be analyzed using intention-to-treat analysis. Multiple imputation will be used to fill missing completely at random and missing at random, and last-observation-carried-forward will be used to fill miss not at random data.

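### Repeated-measures ANOVA is given the task of showing the time course of the effect, but none of its arm-related tests is the arm effect at 3 or at 6 months; a baseline-adjusted model by visit would give it

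*Protocol article*

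**What the plan says.** All references are to the protocol article.

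- **Statistical methods, longitudinal analysis:** "Repeated measurement analysis of variance will be used to analyze the intervention effect at different intervention times". The section does not list the time levels, the term to be tested or how sphericity is handled.
- **Statistical methods, other between-group analyses:** "one-way analysis of variance (ANOVA) and covariance analysis will be used for inter-group comparison", with Bonferroni-corrected pairwise comparisons after the ANOVA. On covariates it says only: "Covariance analysis will be used to control other non-interventional factors". Baseline FVC is not named.
- **Trial design, schedule:** "The main and secondary results will be tested at baseline and at 3 and 6 months after the beginning of the intervention". The Outcomes section gives the same three time points: "All results will be evaluated at baseline and 3 months and 6 months after the intervention by the same evaluator".
- **Outcomes, framing:** "The changes of pulmonary function from baseline to the end of the interventions will be assessed".
- **Sample size calculation:** "the sample size was calculated by one-way ANOVA in Power Analysis and Sample Size version 15.0.5". Its planning values are: "With a power of 80%, an alpha of 0.05, a standard deviation of 48, a standard deviation of the means of 8.16". With 20% dropout this leads to 120 subjects per arm.

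**The concern.** The trial asks which of three modalities improves lung function most. That needs differences between arms at a stated time. The plan gives the time course of the effect to repeated-measures ANOVA, which offers two arm-related tests: a group main effect and a group-by-time interaction. What each one measures depends on whether baseline is a level of the time factor, and the text leaves that open.

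If the main effect were used with baseline as a level, a real effect of the planned size could easily be missed. If the interaction were used, a significant result would not show at which visit, between which arms or in which direction the difference lies. These tests also differ widely in power, and the choice among them stays open until the data are in.

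**Working it through.** **Inputs from the documents.** Four arms; SD 48 (unit not given, and not said whether it is the SD at a visit or of a change); SD of the means 8.16; alpha 0.05; 20% dropout; 120 per arm.

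**Assumptions, because the documents give no figure.** Equal correlation ρ between visits, 0.5 to 0.95. No arm difference at baseline, a fraction h of the planned effect at 3 months (h = 0.5 or 1), and the full planned effect at 6 months. 48 is the SD at a visit unless stated otherwise. Power is from the noncentral F distribution with 96 completers per arm.

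**Step 1: the plan's own figure.** λ = 4 × 96 × (8.16/48)² = 384 × 0.0289 = 11.10, df 3 and 380, power 80.3%. With 95 per arm power is 79.9%, so 96 is the smallest size that reaches 80%, and 96/0.8 = 120. The stated sample size reproduces.

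**Step 2: baseline, 3 and 6 months as levels.**

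Group main effect: λ = 11.10 × ((1 + h)/3)² ÷ ((1 + 2ρ)/3), df 3 and 380.

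Interaction: λ = 11.10 × S/(1 − ρ), df 6 and 760. S is the sum of squared deviations of (0, h, 1) from its mean: 0.500 for h = 0.5 and 0.667 for h = 1.

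| ρ | h | Main effect λ | Main effect power | Interaction λ | Interaction power |
|---|---|---|---|---|---|
| 0.5 | 0.5 | 4.16 | 36.8% | 11.10 | 69.4% |
| 0.5 | 1 | 7.40 | 61.1% | 14.80 | 83.4% |
| 0.7 | 0.5 | 3.47 | 31.1% | 18.50 | 91.7% |
| 0.7 | 1 | 6.17 | 52.6% | 24.66 | 97.7% |
| 0.8 | 0.5 | 3.20 | 28.9% | 27.74 | 98.9% |
| 0.8 | 1 | 5.69 | 49.0% | 36.99 | 99.9% |
| 0.95 | 0.5 | 2.87 | 26.1% | 110.98 | >99.9% |
| 0.95 | 1 | 5.10 | 44.5% | 147.97 | >99.9% |

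If 48 is instead the SD of change, the visit variance times (1 − ρ) equals 48²/2. Interaction power is then 69.4% (h = 0.5) or 83.4% (h = 1) whatever ρ is. The main effect is weaker still, for example 9% at ρ = 0.9 and h = 0.5.

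**Step 3: sphericity, relevant only with three levels.** Type I error of the interaction F from 20,000 simulated null trials per structure (simulation standard error about 0.15 points). Correlations are listed as baseline–3, baseline–6 and 3–6 months.

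| Structure | Epsilon | Uncorrected | Greenhouse-Geisser |
|---|---|---|---|
| 0.8, 0.8, 0.8 | 1.00 | 5.3% | 5.3% |
| 0.5, 0.25, 0.5 | 0.93 | 5.7% | 5.2% |
| 0.9, 0.81, 0.9 | 0.82 | 6.1% | 4.8% |
| 0.9, 0.8, 0.9, SD ratio 1:1:1.3 | 0.72 | 7.4% | 5.1% |
| 0.7, 0.7, 0.95 | 0.63 | 8.0% | 5.1% |
| 0.9, 0.7, 0.9 | 0.61 | 8.6% | 5.2% |

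**Step 4: only 3 and 6 months as levels.** There is one within-subject contrast, so sphericity cannot fail.

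- Main effect: λ = 11.10 × ((1 + h)/2)² ÷ ((1 + ρ)/2). For h = 0.5, λ is 8.32 at ρ = 0.5 and 6.40 at ρ = 0.95, giving 66.8% and 54.3% power. For h = 1, λ is 14.80 and 11.38, giving 91.0% and 81.4%. It estimates the average over the two visits.
- Interaction: λ = 11.10 × ((1 − h)²/2)/(1 − ρ). For h = 1 this is 0, so the test rejects 5% of the time however large the effect is.

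**Step 5: baseline-adjusted comparison at 6 months.** This stands in for the 6-month contrast of the proposed model with complete data; df 3 and 379.

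- 48 as visit SD: λ = 11.10/(1 − ρ²), which is 14.80, 21.76 and 30.83 at ρ = 0.5, 0.7 and 0.8. Power is 91.0%, 98.3% and 99.9%.
- 48 as SD of change: λ = 11.10 × 2/(1 + ρ), which is 14.80 at ρ = 0.5 and 11.68 at ρ = 0.9. Power is 91.0% and 82.5%.

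Both exceed the 80.3% of the unadjusted one-way ANOVA.

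**The case against.** The strongest reply is that the protocol never says baseline is a time level or that an uncorrected F will be used. The visit schedule says when FVC is measured, not what enters the model, and baseline comes before any intervention. This stands: the dilution in Step 2 and the error rates in Step 3 are conditional. An epsilon correction is also a detail that a condensed article may leave to the analysis plan.

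Three stronger readings are tempting, and the documents do not support them.

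- **That repeated-measures ANOVA gives no valid test of the intervention.** With randomised arms, group-by-time including baseline is a valid test of whether change differs, which fits the change-from-baseline framing under Outcomes. Its power is about 92% or more at correlations of 0.7 and above with 48 as visit SD. It falls below 80% only at low correlation, or with 48 as the SD of change, when the effect builds gradually.
- **That the stated power and alpha are wrong.** They belong to the one-way ANOVA, which remains in the plan and reproduces.
- **That the plan offers no comparison between arms.** One-way ANOVA, covariance analysis and corrected pairwise comparisons are planned. Covariance analysis could give the baseline-adjusted contrast if baseline FVC were among its covariates, but it is not named.

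The reply does not rescue the sentence itself. Taking only 3 and 6 months as levels removes the dilution and the sphericity question, yet the two tests then give a visit average and a change in effect. Follow-up comparisons at each visit would be a further step, and the sentence on repeated measures does not name one.

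**Conclusion.** The point holds as an improvement to the method, not as an error in a stated figure. Under either reading of the time levels, no arm-related test of the planned repeated-measures ANOVA is the arm effect at 3 or at 6 months. If baseline is a level, the group main effect has 26–61% power for the effect the trial is sized on, and the interaction is valid but omnibus. The interaction's type I error exceeds 5% (about 6–9% in the non-spherical cases simulated) only if sphericity fails and no correction is made.

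A baseline-adjusted comparison at 6 months uses data already planned. It has 91% power or more with 48 as visit SD and correlation 0.5 or above, and 82.5–91.0% with 48 as SD of change and correlation 0.5–0.9. The correlations, the 3-month effect and the meaning of 48 are assumptions. That the tests do not target the effect at a visit depends on none of them.

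**What to change.** Replace the sentence on repeated-measures ANOVA with wording such as: *FVC at 3 and 6 months will be analysed in a linear mixed model with arm, visit, arm-by-visit, baseline FVC and baseline FVC-by-visit as fixed effects and an unstructured covariance. Bonferroni-adjusted arm differences at 3 and at 6 months will be read from this model.* Baseline then enters only as a covariate.

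If repeated-measures ANOVA is kept as a supplement, name its time levels, use the group-by-time term with a Greenhouse-Geisser correction, and do not interpret the group main effect when baseline is a level.

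The cost is a change of wording and slightly more analysis work. No extra subjects, visits or measurements are needed, and the sample size calculation can stay as it is.

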## Background

Pulmonary function is highly age-dependent, with a slow decline starting at 20–30 years of age [1]. Decreased lung function results in the loss of lung tissue elasticity, reduced chest wall compliance, and reduced area for gas exchange [2]. Even in healthy people, lung function decreases with age [3]. When lung function declines too rapidly, the incidence of related diseases, such as respiratory and cardiovascular diseases, greatly increases [4]. Chronic obstructive pulmonary disease (COPD) is one of the most common diseases presenting with decreased pulmonary function, and the Global Burden of Disease Study 2015 estimated that approximately 174 million people suffer from COPD worldwide [5]. The rapid decline in lung function is also a significant predictor of death [6]. In 2015, COPD was ranked the third cause of age-standardized mortality in men and women globally, with approximately 3.2 million patients dying of the disease [7]. Middle-aged and older people with lower lung function have a faster rate of decline in cognitive abilities, such as memory and executive functions, than those with higher lung function [8]. Research shows that early exercise intervention and care for healthy older people can effectively reduce the incidence of chronic diseases and reduce health care costs [9]. Due to accelerated aging, the population of people aged > 65 in China was projected to reach 400 million by 2050, of which 150 million were above the age of 80 [10]. Therefore, it is very important to intervene in the early pulmonary function of middle-aged and elderly subjects.

Exercise greatly affects health status, and a lack of adequate exercise may cause systemic inflammation, cardiac dysfunction, and decreased lung function leading to most chronic diseases [11–13]. For most healthy adults, the benefits of exercise far outweigh the risks, and regular exercise is beneficial to improve and maintain the health of lung function [14]. For people with respiratory diseases, exercise training is regarded as the cornerstone of lung rehabilitation since it promotes disease rehabilitation, improves postoperative recovery, and prevents complications [13, 15]. Therefore, regular exercise is of great significance for both healthy individuals and those with respiratory diseases. However, the importance of exercise remains overlooked by some doctors and patients [16].

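### Missing FVC values are sorted by a mechanism that the data cannot reveal, and those called not at random are filled by LOCF, which can bias the comparison in either direction

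*Protocol article*

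**What the plan says.** The last paragraph of Statistical methods has three parts:

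- "All missing data will be analyzed using intention-to-treat analysis".
- "Multiple imputation will be used to fill missing completely at random and missing at random".
- For the remainder, "last-observation-carried-forward will be used to fill miss not at random data".

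The section gives no criterion for assigning a missing value to a mechanism, and nothing elsewhere in the article qualifies the rule. FVC is the primary outcome and is measured at baseline, 3 months and 6 months (Trial design; Outcomes), so LOCF can carry only a baseline or a month-3 value to month 6. Sample size calculation plans for 20% dropout.

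**The concern.** There are two faults.

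1. **The sorting step cannot be carried out.** Missing at random and missing not at random differ only in whether missingness depends on the unseen values. No test on observed FVC separates them. Which values go to multiple imputation and which to LOCF is therefore a judgement, made on the primary outcome after data have been collected.

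2. **LOCF does not model data missing not at random.** It assumes that FVC stays at its last measured value, and it treats the filled value as if it had been measured. That fits poorly with the article's own premises. The Background states that "Even in healthy people, lung function decreases with age", and the training is meant to build over 24 weeks (Strategies to improve adherence to interventions). The rule gives this fill-in to the very values for which departure from missing at random is suspected.

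With 20% dropout, about 0.20 × 120 = 24 subjects per arm could come under the rule. The exercise arms attend five supervised sessions a week and the control arm none, so unequal dropout is plausible, though the article does not predict it. A lesser point of wording: intention-to-treat names the analysis set and does not say how missing values are handled.

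**Working it through.** **The plan's own figure.** Inputs from Sample size calculation: four groups, alpha 0.05, SD 48, SD of means 8.16, dropout 20%. The unit is not stated.

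- Effect size f = 8.16/48 = 0.17.
- Noncentral F power: 79.9% with 95 per group, 80.3% with 96.
- 96/(1 − 0.20) = 120 per group, as stated.

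The planned position is therefore 80% power on 96 evaluable subjects per group.

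**Assumptions for the illustrations (not in the article).** Half of the dropouts leave before month 3 and half after; mean change is linear; the SD stays at 48; correlations between visits are 0.80 to 0.85. LOCF then loses, per dropout, the fraction 0.5 × 1 + 0.5 × 0.5 = 0.75 of the 6-month change.

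**A. Equal dropout of 20%, all filled by LOCF.**

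- Fraction of a true difference retained: 1 − 0.20 × 0.75 = 0.85, an attenuation of 15%.
- f becomes 0.17 × 0.85 = 0.1445. Power with 120 per group is 75.8%, against the planned 80%.
- With no true difference, the expected bias is zero.

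**B. No true difference, dropout 25% in an exercise arm and 10% in control, common 6-month change of 24 units (0.5 × 48).**

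If all dropouts get LOCF:

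- Exercise: 24 × (1 − 0.25 × 0.75) = 19.5. Control: 24 × (1 − 0.10 × 0.75) = 22.2.
- Spurious difference: 19.5 − 22.2 = −2.7. With a common decline of 24 the sign reverses to +2.7.
- Type I error in simulated two-arm ANCOVA (120 per arm): about 12%.

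If one third of dropouts get LOCF and the others are left out, as a stand-in for multiple imputation:

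- LOCF share of those analysed, exercise: (0.25/3)/(0.75 + 0.25/3) = 0.100. Control: (0.10/3)/(0.90 + 0.10/3) = 0.036.
- Bias in size: (0.100 − 0.036) × 0.75 × 24 ≈ 1.2 units. Type I error: about 6%.

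**C. Dependence on the common change** (same 25% and 10% dropout):

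| Common change | Share given LOCF | Type I error |
|---|---|---|
| 0 | all | about 5% |
| 10 units | all | about 6% |
| 24 units | one third | about 6% |
| 24 units | all | about 12% |
| 48 units | one third | about 9% |
| 48 units | all | 25% to 28% |

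**D. Dropout that is truly not at random.** Here poor responders leave (1 logit per SD of change), the SD of change is 48, the correlation between month-3 and month-6 change is 0.5, and there is no true difference. With dropout of 30% in the active arm and 10% in control, LOCF gives a spurious +4.5 if baseline is carried and +2.2 if month 3 is carried. With the rates reversed it gives −4.6 and −2.3. Completers alone give +7.7 and −7.8.

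**The case against.** The strongest reply concerns size. The plan sends only part of the missing data to LOCF, and that part is unknown. The larger error rates need every dropout filled by LOCF, an assumed 25% against 10% split, and a common change of 0.5 to 1 SD within 6 months. The Background speaks only of a slow decline, and the repeat-manoeuvre rules under Primary outcome measurements work against a large learning effect. Telephone follow-up and attendance checks may limit dropout. All of this stands, and it makes those figures a worst case.

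A reader might also infer four stronger things that the article does not support:

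- **That LOCF certainly biases the result.** With equal dropout and no true effect the expected bias is zero. Nor did treating filled values as measured raise the error rate by itself in these simulations: with no common change it stayed near 5%.
- **That an analysis of observed cases would be safe.** It held 5% only where dropout was random within arm. In simulations where poor responders left, with no true effect, observed-case ANCOVA had type I error of about 13% to 15%, against about 5% to 9% for LOCF. This does not vindicate LOCF, but it shows that no single method is safe under that mechanism.
- **That power falls from 89% to 76%.** The 89% is for 120 complete subjects per arm. The plan promised 80%, so the loss is about 4 points.
- **That the analyst could steer the result.** Randomization and blinding states that the data analyst is blinded. This limits deliberate steering but does not make the mechanism identifiable.

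None of these points makes the sorting rule workable or turns LOCF into a method for data missing not at random.

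**Conclusion.** The rule is wrong as stated and should be changed before the data are seen. It does not by itself invalidate the trial. The sorting cannot be done objectively, and LOCF puts an assumption of no change where a departure from missing at random is suspected.

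The effect on the FVC comparison can go either way. Across the illustrations for the stated rule, it runs from nothing to 2.7 units at a common change of 24, and a true difference is attenuated by about 15% when a uniform 20% dropout is filled entirely by LOCF. These sizes rest on assumed dropout splits, trajectories and LOCF shares, so they show what the rule permits and do not predict the result. They are best read against the SD of 48: converting the SD of means of 8.16 into a planned difference between arms requires a pattern of means that the article does not give.

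**What to change.** Delete both the sorting by mechanism and LOCF. In their place:

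- **Primary analysis.** Handle all missing FVC under one stated missing-at-random assumption. Use either multiple imputation by arm from baseline and month-3 FVC, or a mixed model for repeated measures on all randomised subjects. Name one of the two in advance.
- **Sensitivity analyses for data missing not at random.** Prespecify reference-based imputation and a delta-adjusted tipping-point analysis. They are needed because the primary analysis is not itself unbiased if data are missing not at random.
- **Wording.** Use intention-to-treat for the analysis set only.

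Multiple imputation is already planned, so the cost is a change of wording and a little extra programming. No further subjects or measurements are needed, and the sample size stays at 120 per group.
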